### Acceptance and commitment therapy (ACT) [26]

ACT is a newer form of cognitive behaviour therapy that aims to engender a quality called ‘psychological flexibility’, which can be defined as: ‘… the capacity to persist or to change behaviour in a way that includes conscious and open contact with thoughts and feelings (openness), appreciates what the situation affords (awareness), and serves one’s goals and values (engagement).’ Consequently, within an equal, warm relationship, a clinician will carefully offer a range of therapy methods and techniques to enhance psychological flexibility. For example, a clinician might help a person connect with their own over-arching goals and values by having conversations that enable a deeper understanding of how they want to be in their key relationships. A therapist may then help them find ways to include more activities that are consistent with these values into their everyday life. Willingness, self-compassion or de-centring exercises may then be explored as ways to approach the challenging thoughts and feelings that often accompany making important changes or doing new things.

### Psychodynamic interpersonal therapy (PIT)

This is a psychodynamic form of therapy which aims to manage feelings in the context of interpersonal relationships. It focuses upon interpersonal problems or ways of relating which may underpin symptomatic or problem scenarios. There is a strong focus on developing a strong therapeutic alliance from which interpersonal problems can be identified and solved. The different components of the model are as follows: (1) focus on feelings, (2) encourage the client to stay with feelings, (3) explore what associated thoughts, images, memories come to mind, (4) explore links or patterns in interpersonal relating that are problematic, (5) acknowledge these problematic patterns, (6) test out new ways of behaving both in the session with the client and in personal relationships outside. A goodbye letter is given to the client at the end of the therapy to summarise the work.

### Criteria for discontinuing or modifying allocated interventions {11b}

The intervention will be discontinued at the discretion of the therapist and clinical team if they judge the participant to be at increased risk of harm by continuing with therapy or if the participant wishes to withdraw. Participants can discontinue and/or withdraw from the study intervention at any time and will follow the same data collection follow-up schedule unless they withdraw from such aspects of the study.

The site clinician or therapist/supervisor may recommend that the participant be withdrawn from further active follow-up such as sending of SMS messages and/or questionnaires; however, it is expected for such instances to be rare and the default position will be for follow-up and data collection to continue.

### Strategies to improve adherence to interventions {11c}

To maximise intervention delivery, therapy can be delivered face to face or online. Therapist training, fidelity assessment and supervision aim to improve adherence to the intervention manual. All therapists will undertake a competency check as part of their training and as a prerequisite for delivering therapy.

Fidelity to each of the interventions will be measured, including fidelity to the self-harm adapted approach, and to each of the three psychological therapies (CBT, PIT and ACT). Inclusion of the key ingredients of the self-harm adaptation will be recorded for the first assessment session of each therapy.

Participants’ adherence to the intervention will be recorded by the number of sessions offered and attended, participants completing therapy and reasons for ending therapy. All data will be recorded by therapists via CRF.

All therapy sessions in the intervention arm of the trial will be audio-recorded. Fidelity assessments will be made via a therapist-reported checklist of content for all sessions and through researcher rated assessment of audio recordings of therapy sessions. These checklists are available as additional files (file numbers 2, 3 and 4). Fidelity will assess the following components of the intervention:Adaptations for working with people who self-harm in the initial assessment and subsequent sessions, specific to the FReSH START approach and common across the modified therapiesFidelity to the individual psychological therapeutic approach. In ACT, for example, therapy will be reviewed by an expert who is external to the trial using the Acceptance and Commitment Therapy Fidelity Measure (ACT-FM) [27]

The ratings of the FReSH START approach (available as Additional file no. 5) will be conducted on the initial sessions (sessions 1–3). A random sample of 10% of the first session of therapy, stratified by therapist and centre, will be reviewed and scored using the fidelity measure. The rater will have the option of listening to sessions two and three of the same therapy to complete their assessment as not all parts of the FReSH START approach may be completed in session one (for example safety planning may extend over sessions 1–3). We estimate 32–96 sessions will be rated representing 32 different therapists.

Assessment of the individual psychological therapeutic approach will be made using items from therapy-specific scales: the Sheffield Psychotherapy Rating Scale for PIT (Additional file no.2) and CBT (Additional file no. 3) and the ACT Fidelity measure for ACT (Additional file no.4). To assess competency of delivery for the first five therapists in all three therapy modalities, the fourth therapy session delivered will be appraised for its fidelity to the relevant therapy. These reviews will be conducted by the relevant member of the research team. If at this point the fidelity is deemed appropriate, no further assessment will take place. If, however, fidelity to the relevant therapy is not fulfilled, another check will take place after the seventh delivered session and if problems persist again after the ninth. If the fidelity check still fails after the ninth session, the therapist will not be allocated further trial participants, though consideration will be given regarding participants who may provide a particular challenge, making it difficult for the therapist to demonstrate adherence. If the competency assessment on the first five therapists of each modality all pass, the trial researchers can be assured that the training and assessment strategy for each modality is working. If persistent problems are identified, further therapists beyond the first five may have to be considered for competency.

Assessment of the individual psychological therapeutic approach will be made using items from therapy-specific scales: the Sheffield Psychotherapy Rating Scale for PIT and CBT and the ACT Fidelity measure for ACT. Assessment will be performed by a therapist with expertise in the relevant therapy. Approximately 5% of sessions will be randomly sampled, excluding the first three sessions as these are less likely to contain therapy specific interventions. An estimated 140 sessions will be rated.

Additionally, for the first five therapists in all three therapy modalities, the fourth therapy session delivered will be appraised for its fidelity to the relevant therapy. If at this point the fidelity is deemed appropriate, no further assessment will take place. If, however, fidelity to the relevant therapy is not fulfilled, another check will take place after the seventh delivered session and if problems persist again after the ninth. If the fidelity check still fails after the ninth session, the therapist will not be allocated further trial participants, though consideration will be given regarding participants who may provide a particular challenge, making it difficult for the therapist to demonstrate adherence. If the fidelity checks on the first five therapists of each modality all pass, the trial researchers can be assured that the training and assessment strategy for each modality is working. If persistent problems are identified, further therapists beyond the first five may have to be considered for assessment.

### Relevant concomitant care and intervention that are permitted or prohibited during the trial {11d}

Participants in both arms of the trial will be offered standard care as delivered in their study site. Participants must not receive another form of individual talking therapy during the intervention study period but can be referred to any other relevant services (e.g. community support groups, alcohol or drug services).

### Provisions for post-trial care {30}

Post-trial care of participants will be usual care offered by their healthcare organisation.

### Outcomes {12}

The primary outcome measure is the difference between the two randomised groups in mean CORE-OM score at 12 months [28]. The CORE-OM is a 34-item measure, widely used in primary and secondary care services in the NHS to assess levels of psychological global distress across four dimensions of well-being, symptoms (depression, anxiety, physical and trauma), functioning and risk [28]. Quality of life (QoL) is the most important patient-centred outcome as it can capture positive life changes—although reduction in the episodes of self-harm would be expected, one does not necessarily mediate the other. Secondary outcome measures include the Social Connectedness Scale (SCS) [29], the Beck Hopelessness Scale [30] and the PHQ-9 [31]. The SCS has been included as we argue that a valued goal is interpersonal in nature; therefore, achieving this through means other than self-harm will lead to more positive social connections which we know is associated with quality of life [32]. The PHQ-9 provides a reliable and valid measure of depression severity, and the Beck Hopelessness Scale as hopelessness has been shown to be a risk factor in suicidal behaviour [33].Secondary outcomes measures assessed at 6 and 12 months post randomisation (unless otherwise indicated) include difference in mean score on the CORE-OM at 6-months;Difference in the proportion of participants with reliable and clinically significant improvement on the CORE-OM (defined as a change of five or more in the clinical score and a change in score from the clinical to non-clinical range);Difference in mean score on the Beck Hopelessness Scale (BHS) [30], a 20-item self-report inventory used to measure feelings about the future, loss of motivation, and expectations;Difference in mean score on the Patient Health Questionnaire- 9 (PHQ-9) [31], a 9-item self-report measure of depression severity used to assess mental and emotional conditions;Difference in mean score on the Social Connectedness Scale—revised (SCS-R) [29], a 20-item scale used to measure social connectedness as a sense of belonging;Difference in rates of self-reported self-harm repetition measured monthly using questionnaires and also using monthly SMS messages for the 6-month follow-up period;Difference in the time to repetition of self-harm leading to hospital attendance using routinely collected data from Hospital Episode Statistics (A&E, emergency care, admissions, and outpatient datasets).

Health economic evaluation outcome measures.Quality-adjusted life years (QALYs) [34], generated via the CORE-6D preference-based measure based on six CORE-OM questions;Self-reported resource use from the NHS (primary and community care, medications) and patient (employment and financial costs due to self-harm) perspectives.

### Participant timeline {13}

This protocol follows the Standard Protocol Items: Recommendations for Interventional Trials (SPIRIT) guidelines and meets the SPIRIT checklist.

### Sample size {14}

The recruitment target is 565 participants equally distributed across standard care and intervention plus standard care. This will provide 90% power at 5% significance to detect a between-group difference of three points on CORE-OM (standardised effect size of 0.375) allowing for 25% loss to follow-up and design effect of 1.56. The design effect appropriately inflates the required sample size for an individually randomised controlled trial to account for clustering resulting from therapist-delivered intervention. The design effect assumes (i) cluster size of 11—on average each of 21 intervention therapists treat 15 patients, 11 provide follow-up data; (ii) coefficient of variation of 1.34 to account for variable numbers of patients per therapist (range 3–23) and (iii) intervention intra-cluster correlation coefficient (ICC) of 0.05 [35].

A similar design effect is assumed within the control arm: a wider range of therapists provide treatment as usual, resulting in fewer trial patients per standard care therapist (smaller cluster size) but potentially a higher ICC.

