**Methods:**

FReSH START is a multicentre individually 1:1 randomised controlled trial evaluating the clinical and cost-effectiveness of standard care plus psychological therapy or standard care alone for adults (≥ 18 years) presenting at an emergency department (ED) with repeated self-harm. Recruiting 630 participants, it includes an internal pilot, economic evaluation and process evaluation. The intervention will be delivered by mental health staff working in acute settings, with experience of assessing and managing risk in people presenting to emergency services with self-harm. Staff will be trained and supervised to deliver one of three specially adapted therapies: psychodynamic interpersonal therapy, cognitive behavioural therapy or acceptance and commitment therapy. Participants allocated to the intervention will receive one of the adapted therapies according to therapist allocation for up to 6 months via 12 weekly, one to one, 45–50-min sessions. The primary outcome is quality of life measured by the Clinical Outcomes in Routine Evaluation Outcome Measure at 12 months post-randomisation. Secondary outcomes include suicidal intent, depression and cost-effectiveness. Data are collected using hospital attendance records and online/postal/telephone questionnaires at 6 and 12 months post-randomisation, with resource use additionally collected at 3 and 9 months.

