### Recruitment {15}

The trial plans to recruit from 12 to 14 sites over 36 months. The sample size of 565 requires that each site will recruit an average of 41 participants. Assuming the majority of sites recruit for a 24-month period due to staggered set-up, sites will recruit on average 2 participants per month.

An internal pilot will assess progression criteria on recruitment rates at nine months from the start of recruitment. Rates will be calculated from recruitment in each of the six sites in months 4 to 9 to allow time for recruitment to stabilise. The average number of participants recruited per month will be assessed as: red if < 12, amber if 12–19 and green if ≥ 20. Assuming six sites are open to recruitment, the criteria would be approximately equivalent to assessing monthly recruitment per site as: red if < 2, amber if 2–3.2, green if ≥ 3.3 participants per site per month. The internal pilot will inform a decision on continuation or modification of the trial, with an additional 9 months of recruitment anticipated thereafter. If the recruitment criterion is amber, we will review trial processes comprehensively, with the TSC and the funder, to see if modifications could be made to improve recruitment rates. If the recruitment criterion is red, the TSC and the funder will consider not continuing the trial.

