## Statistical methods

### Statistical methods for primary and secondary outcomes {20a}

A detailed statistical analysis plan will be finalised and agreed by the research team prior to analysis.

A single final analysis is planned after the trial is closed to recruitment and follow-up and when the full database has been cleaned and locked. Analyses will be completed by the CTRU statisticians using SAS version 9.4.

The primary analysis of CORE-OM will use mixed multilevel linear regression with repeated measures (6- and 12-month outcome) adjusted for randomisation stratification factors and baseline value, with therapist treated as a random intercept. Estimated mean treatment differences at each time point will be reported with 95% confidence interval, *p*-values and ICCs. A two-sided 5% significance level will be used for statistical endpoint comparisons, unless otherwise specified.

Secondary outcomes, reliable and clinically significant improvement on the CORE-OM, hopelessness, depression and social connectedness will be analysed using the same approach, i.e. mixed multilevel linear or logistic regression, depending on the type of outcome variable.

Secondary outcomes repetition of self-harm leading to hospital and self-reported repetition of self-harm will be analysed separately.

Cox proportional hazards, accounting for randomisation stratification factors and random therapist effect (multilevel survival frailty model) [40], will be used to test for differences in the time to first repetition and the proportion of participants attending hospital for self-harm at 6 and 12 months. Hazard ratios and corresponding 95% CIs will be presented. If a participant is lost to follow-up, they will be treated as censored. Kaplan–Meier curves will be constructed for each group.

Recurrent event analysis incorporating the timing and cumulative number of hospital attendances for self-harm will be used to test for differences in the rate of recurrent events. Estimated treatment differences will be reported as the hazard ratio with 95% confidence interval and *p*-values.

Self-reported self-harm will be summarised at each follow-up time point (monthly to 12 months).

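### The stated inputs need about 622–628 participants for 90% power; the 565 they are attached to gives about 87%, and the printed therapist layout and the abstract both point to 630

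*Protocol article*

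**What the plan says.** The Sample size section of the protocol article gives the target and its power claim: "The recruitment target is 565 participants equally distributed across standard care and intervention plus standard care", followed by "This will provide 90% power at 5% significance to detect a between-group difference of three points on CORE-OM". The standardised effect is 0.375. The same sentence allows for 25% loss to follow-up and a design effect of 1.56. The design effect is described through three components:

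- cluster size: "on average each of 21 intervention therapists treat 15 patients, 11 provide follow-up data";
- a coefficient of variation (CV) of 1.34 for patients per therapist, with a range of 3–23;
- an intra-cluster correlation (ICC) of 0.05.

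A similar design effect is assumed in the control arm.

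The Recruitment section repeats the target: "The sample size of 565 requires that each site will recruit an average of 41 participants". The abstract gives another: "Recruiting 630 participants, it includes an internal pilot, economic evaluation and process evaluation". The Trial status section gives a third. Clustering was re-estimated in autumn 2023, and in February 2024 the funder, supported by the Programme Steering Committee, agreed a revised minimum of 348. That section does not give the re-estimated design effect.

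**The concern.** The power statement supplies every input that it needs, so it can be recomputed. The result is not 565. The abstract's total and the therapist layout agree with each other, and both disagree with the total beside which the layout is printed.

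At stake is the justification for the primary comparison. On the stated inputs the type II error at 565 is about 13%, not the 10% claimed. The article carries three totals (630, 565 and 348). Only 565 has assumptions printed with it, and it does not follow from them. A reader who wants to judge the later reduction to 348 has no sound starting calculation.

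**Working it through.** **Inputs**

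- Effect 0.375, 90% power, 5% significance, 25% loss, design effect (DE) 1.56 in both arms: Sample size section.
- Two-sided: "A two-sided 5% significance level will be used for statistical endpoint comparisons, unless otherwise specified", from the statistical methods section {20a}.
- 1:1 allocation: Sequence generation section {16a}.

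**Step 1. Try to reproduce 565**

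Per arm, without clustering or loss:

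n = 2(1.960 + 1.282)² / 0.375² = 149.4 (150 rounded up). A t-based calculation gives 150.4 (151 rounded up).

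Total N = 2n × 1.56 / 0.75:

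| Method | 2n | Total N |
|---|---|---|
| Normal, unrounded | 298.9 | 621.7 |
| Normal, rounded up | 300 | 624.0 |
| t-based, unrounded | 300.8 | 625.7 |
| t-based, rounded up | 302 | 628.2 |

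So 565 is not reproduced; it is 9–10% below the requirement.

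**Step 2. Power at each total, with DE 1.56**

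Effective n per arm = N × 0.75 / 1.56 / 2. Normal power = Φ(0.375 × √(n/2) − 1.960).

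| N | Effective n per arm | Normal | t-based |
|---|---|---|---|
| 565 | 135.8 | 87.1% | 86.8% |
| 630 | 151.4 | 90.4% | 90.2% |

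**Step 3. Therapist layout**

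- As printed: 21 × 15 = 315 in the intervention arm, and 315 × 2 = 630. Followed up: 15 × 0.75 = 11.25, which fits the stated 11.
- At 565: 282.5 / 21 = 13.5 per therapist, and 13.5 × 0.75 = 10.1 followed up. Neither matches the printed 15 and 11.

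**Step 4. Other conventions, keeping DE 1.56**

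- One-sided 5%: 507.
- Clustering in the intervention arm only (average DE 1.28): 510. The plan rules this out.
- Loss as × 1.25 instead of / 0.75: 583–589.

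None gives 565. It appears only if a stated input changes: DE = 565 × 0.75 / 2n = 423.75 / 300.8 = 1.41 (1.42 with 298.9), or DE 1.5 combined with the incorrect × 1.25 for loss (560–566).

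**Step 5. The design effect itself**

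The usual formula for unequal clusters is DE = 1 + [(1 + CV²)m − 1] × ICC.

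- Printed components: 1 + [(1 + 1.34²) × 11 − 1] × 0.05 = 2.49.
- For 1.56, the CV would have to be about 0.33–0.34 (these give 1.560 and 1.564).
- At DE 2.49, power is about 68–69% at 565 and 73% at 630.

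This is a separate inconsistency. It does not rescue 565, and it means that 630 fits the stated DE of 1.56 but not the printed CV.

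**Step 6. Per-site average**

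565 / 14 = 40.4, so an average of 41 roughly fits 565 at 14 sites. At 630 it would be 630 / 14 = 45.

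**The case against.** The strongest reply is that neither 565 nor 630 is now the working target. The Trial status section reports the agreed minimum of 348, with 266 recruited by 30 June 2024 and recruitment expected to end on 30 September 2024. The error therefore sits in a planning statement already overtaken within the same article. This stands as a limit on the practical consequence. It does not explain 565, which the Sample size section still ties to DE 1.56 and 90% power.

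Second, 565 may rest on other clustering inputs. The Trial status section expects a gain in power because more therapists were trained than assumed, and the fidelity section refers to 32 therapists. On that account the fault lies in the description and not in the trial's power. The documents leave this open, since they give no alternative inputs for 565.

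Third, a lower therapist load also lowers the design effect. With 10.1 followed up per therapist, ICC 0.05 and an assumed CV of 0.33–0.34, DE is about 1.51 and power at 565 is 87.8–88.1%. The shortfall narrows to about 2 points but does not close.

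A reader might also infer that 565 was put in place of 630 while the older assumptions were left standing. That is plausible, but no section says so. Nor do the documents support reading this as a call to recruit 630: that would reinstate a total above the one that the funder agreed.

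**Conclusion.** The power statement is wrong as written. With effect 0.375, two-sided 5%, 25% loss and DE 1.56 in both arms, 90% power needs about 622–628 participants. At 565 power is about 87%, roughly 3 points short, and the type II error is about 13% instead of 10%. The abstract and the printed layout both point to 630.

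The result takes the stated 1.56 as given, and the printed CV contradicts that figure. A reader might infer that actual power is 68–69%. That follows only if the CV of 1.34 is right and the 1.56 is wrong, and the documents do not settle which is in error. Nor does this show that the trial is underpowered at its revised target, because the re-estimated clustering behind 348 is not given.

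**What to change.** In the Sample size section, do one of the following:

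1. Keep 565, state about 87% power at DE 1.56, and correct the load to about 13.5 patients per therapist, about 10 followed up.
2. Keep 565 and 90%, and print the clustering inputs that justify it (DE about 1.41).

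With either option:

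- Correct the CV, or the 1.56, so that the components reproduce the design effect. Option 1 is not sound until this is done, and if the design effect or cluster size changes, the power must be recomputed.
- Describe 630 as the calculation for the printed layout of 21 therapists with 15 patients each. Call it the original calculation only if the trial team confirm this, and do not present it as a target to reinstate.
- Make the abstract, the Sample size section and the Recruitment section consistent, and refer in each to the minimum of 348.
- Leave the per-site average of 41 as it is if 565 is kept with 14 sites.

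The cost is wording and one recalculation, with no change to the design. Under option 1 the stated power becomes slightly less favourable.
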